## Abstract

**Introduction:**

Self-management is deemed the cornerstone in overall diabetes management. Web-based self-management interventions have potential to support adults with type 2 diabetes (T2DM) in managing their disease. Owing to somewhat ambiguous results of such interventions, interventions should be theory-based and incorporate well-defined counselling methods and techniques for behavioural change. This study is designed to assess the effectiveness of a theory-driven web-based Guided Self-Determination (GSD) intervention among adults with T2DM in general practice to improve diabetes self-management behaviours and glycosylated haemoglobin (HbA1c).

**Methods and analysis:**

A complex intervention design based on the framework of the UK Medical Research Council is employed as a guide for developing the intervention, assessing its feasibility and evaluating its effectiveness. The study consists of three phases: (1) the modelling phase adapting the original GSD programme for adults with T2DM, using a qualitative design, (2) feasibility assessment of the adapted intervention on the web, employing qualitative and quantitative methods and (3) evaluating the effectiveness of the intervention on diabetes self-management behaviours and HbA1c, using a quasi-experimental design. The first phase, which is completed, and the second phase, which is underway, will provide important information about the development of the intervention and its acceptability, whereas the third phase will assess the effectiveness of this systematically developed intervention.

**Ethics and dissemination:**

The Norwegian Regional Committee for Medical and Health Research Ethics (REK west number 2015/60) has approved the study design. Patients recruited in the different phases will fill out an informed consent form prior to inclusion and will be guaranteed anonymity and the right to withdraw from the study at any time. The results of the study will be published in peer-reviewed journals, electronically and in print, and presented at research conferences.

**Trial registration number::**

NCT02575599.

Strengths and limitations of this studyUse of a complex intervention design.Developing a theory-based Guided Self-Determination programme for adults with type 2 diabetes (T2DM).Testing a web-based intervention in general practice in order to increase self-management among adults with T2DM.The assignment of patients to the intervention and control groups will not be random.The quasi-experimental design requires cautiousness about drawing inferences and conclusions from the data.

## Introduction

Type 2 diabetes (T2DM) is a chronic disease and a growing public health problem worldwide. Its prevalence is increasing rapidly in many countries, including Norway.^1^ In Norway, general practitioners (GPs) and registered nurses working with GPs have traditionally been responsible for the care of T2DM. In addition to annual check-ups and regular consultations (3–4 times a year) with GPs, most people with T2DM are offered a structured educational programme at the hospital on diagnosis to learn how to manage their disease.^2^ Yet, research indicates that only one of eight patients with T2DM achieves the recommended treatment goals of glycaemic control, cholesterol and blood pressure.^3^ Consequently, there is ample room to improve diabetes care.

At present, there is no cure for T2DM. Self-management of the disease is, therefore, a key factor in achieving adequate blood glucose control and preventing long-term complications.^4^ Besides, it is deemed the cornerstone of overall diabetes management.^5^
^6^ Diabetes self-management is described as an active, proactive and ongoing process that includes behaviours such as healthy eating, regular physical activity, blood glucose monitoring and medication taking, as well as problem-solving and healthy coping.^4^ Achieving appropriate self-management is, however, complex.^5^
^7^ Owing to this complexity, research has indicated that individuals consider attainment of treatment goals challenging, and many individuals fail to achieve optimal treatment outcomes.^8^ Given the fact that adults with T2DM implement the majority of self-management tasks,^9^ these tasks need to be facilitated by support from healthcare professionals.^10^ Such support is required for implementing and sustaining coping skills and behaviours needed to self-manage on a continuing basis.^11^ However, a Norwegian study has suggested that support from healthcare practitioners has a weak influence on self-management behaviours.^12^

To promote daily self-management for adults with T2DM, several educational and behavioural programmes have been developed. Moreover, national standards for diabetes self-management education (DSME) and support have been designed to serve as a guide for diabetes educators.^13^ Yet, reviews have demonstrated moderate effects of a number of previous interventions to improve self-management.^7^
^14^ However, a recent review shows that it is important to include support components to best train people in their self-care.^15^ Thus, ongoing educational, behavioural and clinical support is needed following DSME to sustain changes made during DSME.

The internet has increasingly been used for delivering interventions designed to promote self-management and health behaviour change.^16–18^ Reviews investigating a number of web-based interventions for promoting self-management of T2DM have demonstrated substantial improvements in health behaviours such as self-monitoring, physical activity and diet, as well as health-related outcomes such as weight, glycaemic control and emotional distress,^16^
^17^
^19^ whereas other studies have demonstrated moderate effects.^19^
^20^ Owing to these somewhat ambiguous results, it has been suggested that future internet interventions should be theory-based and incorporate counselling methods and techniques for behavioural change.^17–19^ Research has also demonstrated that internet self-management support without tailored feedback has been associated with greater dropout than when provided in combination with tailored feedback.^21^ In addition, previous research has suggested that diabetes self-management support for adults with T2DM is effective when delivered in a community context.^5^ Furthermore, web-based interventions in community-based general practice seem to be convenient, easily accessible and less costly,^22^ and may increase interest and participation in diabetes management that are needed in adults with T2DM.^23^

There is still potential for the development of effective and reliable web-based self-management interventions. In this study protocol, we respond to these challenges by describing the development of a web-based Guided Self-Determination (GSD) programme for adults with T2DM in general practice. The GSD programme has a theoretical foundation in Self-Determination Theory^24^ as well as empowerment^25^ and life-skills theories.^26^ It is designed to be a self-management support programme and has been effective in individual and group training of adults with type 1 diabetes (T1DM).^27^ Moreover, research has demonstrated that application of GSD for people with T1DM in a clinical context has been approved by patients. It is also suggested that GSD can be adapted to other contexts with other patient groups.^28^
^29^ Since T2DM is different from T1DM regarding pathophysiology, symptoms, treatment and diabetes self-management, it is timely to consider how a web-based GSD intervention for adults with T2DM might improve self-management behaviours and subsequent healthcare outcomes in a general practice. To the best of our knowledge, this approach has not yet been investigated.

In this study, we present a study protocol for (1) developing a web-based GSD programme adjusted for adults with T2DM, (2) assessing its feasibility and (3) evaluating its efficacy in general practice.

### Aim

The overall aim of this study is to assess the effectiveness of a web-based GSD programme among adults with T2DM in general practice in order to improve diabetes self-management and glycosylated haemoglobin (HbA1c) through enhanced patient activation, self-management competence and autonomy.

## Methods and analysis

### Study design

We use the framework of complex interventions proposed by the UK Medical Research Council (MRC)^30^
^31^ as a guide for developing the intervention, assessing its feasibility and evaluating its effectiveness. This framework is recommended for the development of interventions containing several interacting components.^30^ The development of the web-based intervention is informed by literature reviews of existing web-based interventions^16^
^17^
^19^ and previous experience in developing, testing and evaluating the GSD among adults with T1DM.^27^

### Study overview

The study detailed in this protocol consists of three phases covering the first three stages of the MRC framework:^30^ (1) the modelling study, which has already been completed, (2) the feasibility study, which started in spring 2016 and is underway and (3) the evaluation study, which is planned to start in 2017. An overview of the different phases containing aims, methods and participants, respectively, is depicted in table 1.

**Table 1 BMJOPEN2016013026TB1:** Study overview

Phases	Aims	Methods	Participants
Phase 1. The modelling study	*Step 1*: Identifying areas to be changed from the original GSD. *Step 2*: Adapting the GSD to patients with T2DM, and for internet delivery.	Qualitative approaches with individual interviews in both steps, using qualitative content analysis. A resource group (12 in total) together with a group of user representatives (5 in total) identified adjustments applicable to adults with T2DM and for internet delivery.	*Step 1*: Eight patients with T2DM recruited from GPs. *Step 2*: Eight patients with T2DM recruited from GPs.
Phase 2. The feasibility study	Pretesting the adapted GSD intervention on the web and assessing its feasibility.	Quantitative: Pre–post design. Qualitative: Individual interviews at the end of the programme, using qualitative content analysis.	40 patients with T2DM who have participated in the web-based GSD adapted for T2DM will be recruited from GPs.
Phase 3. The evaluation study	Evaluating the effectiveness of a structured theory-driven web-based GSD intervention on self-management behaviours and HbA1c.	Quasi-experimental design with outcome assessments at baseline, end of programme and 6-month postprogramme.	A total of 172 patients with T2DM will be recruited from GPs (intervention group n=86, control group n=86).

GP, general practitioners; GSD, Guided Self-Determination; HbA1c, glycosylated haemoglobin; T2DM, type 2 diabetes.

### Phase 1: the modelling study

#### Training the nurses to deliver GSD

We invited four nurses working in different general practices and with extensive experience in counselling patients with T2DM to participate in a structured and supervised training programme to develop their counselling skills in nurse-led consultations. Three of the nurses had formal postgraduate education in diabetes care and the fourth had long experience in diabetes care. The training programme included a 4-day course in the original GSD approach developed for people with T1DM over a period of 9 months. It addressed theoretical and practical topics and employed the method in face-to-face consultations with adults with T2DM. The training also included use of several structured reflection sheets. The development of these sheets was inspired by Arborelius and Bremberg^32^ and based on grounded and selected formal theories.^33–35^ The nurses were trained in three advanced professional communication skills: mirroring, active listening and values clarification response.

#### Description of the original GSD intervention

The original GSD programme consisting of 7 face-to-face consultations with 21 structured reflection sheets was designed to guide patients and professionals through mutual reflections illustrated on semistructured worksheets. Reflections recorded on worksheets are intended to empower the patient to become self-determined, with adequate life skills to manage challenges in diabetes self-management. An overall challenge or problem was reflected on in a central sheet called dynamic judgement building inspired by Bos.^34^ The reflection sheets encompass four themes about the patient–provider relationship, life with diabetes, the relationship between ideal and reality and change work. It is a six-stage process, including (1) the establishment of a mutual relationship with clear I–you-borders, (2) self-exploration, (3) self-understanding, (4) shared decision-making, (5) action and (6) feedback from action. Prior to the consultations, the worksheets are introduced with the purpose of stimulating the patient's reflection processes between the consultations and of preparing for the next consultation.^27^
^36^
^37^

#### Adjusting the GSD programme to patients with T2DM in two steps

The intention of the modelling study was to guide the adjustment of the GSD intervention for web-based delivery to patients with T2DM.^30^ The phase consisted of two steps (table 1). At the initial step, it was essential to identify areas that needed to be changed from the original GSD intervention. As part of the training programme noted above, each of the nurses recruited two patients with T2DM from their general practices to participate in seven face-to-face consultations using the semistructured reflection sheets. The inclusion criteria were: (1) diagnosed with T2DM, (2) adults aged ≥18 years, (3) disease duration >3 months and (4) ability to communicate in Norwegian. After participating in the seven face-to-face consultations, patients were interviewed individually about their experiences with the GSD approach, how it worked for them and potential suggestions on how to tailor-make the approach more appropriate for T2DM. The findings of these interviews were analysed using qualitative content analysis.^38^ A resource group (12 in total) was established with 5 researchers, 3 nurses experienced in using the GSD for people with T1DM and 4 nurses carrying out the intervention (table 1). In addition, to provide patients' perspectives on self-management support, a five-person group of user representatives—two people with T2DM selected from the Norwegian Diabetes Association, two nurses and one GP experienced with working with adults with T2DM—was involved in the discussions. Analyses from the discussions were based on findings from the interviews, experiences from the nurses conducting the programme and perspectives of the users about the relevance of the suggested adjustments. Through this process, the number of face-to-face consultations was reduced from seven to four to make it more time efficient. In addition, the number of worksheets to be used at each consultation was reduced. Since it was important to maintain the essential elements of the GSD, we included the central work sheets on dynamic judgment of current and future problem solving. Table 2 illustrates the number and the content of the reflection sheets used in the intervention for T2DM.

**Table 2 BMJOPEN2016013026TB2:** The GSD adapted to T2DM

The first session	Preparing for subsequent consultations: Invitation to work together The HbA1c measurement
Consultations:	Reflection sheets (RS)
Your life with diabetes	RS 1a. Important events and periods in your life RS 1b. At present, what do you find difficult about living with diabetes? RS 1c. Unfinished sentences—your needs, values, habits and opportunities RS 1d. A picture, metaphor or expression of your life with diabetes
Focus for change	RS 2a. Room for diabetes in your life RS 2b. Your plans for changing your way of life
Work with changes	RS 3a. Clarification of challenge in your life with diabetes RS 3b. Previous problem-solving: thoughts, feelings, goals and actions RS 3c. Dynamic problem-solving
Changes in daily life	RS 4a. Blood sugar checks and your reasons for checking RS 4b. New strategies and long-term plan for change RS 4c. Dynamic judgement of current and future problem solving RS 4d. ‘Pros and cons’

GSD, Guided Self-Determination; HbA1c, glycosylated haemoglobin; T2DM, type 2 diabetes.

In the second step, the same nurses each recruited two additional patients with T2DM from their general practices according to the same inclusion criteria mentioned above. After participating in the four face-to-face GSD consultations adapted for T2DM, patients were interviewed individually about their experiences with the adapted approach. Preliminary findings from the interviews indicated that the patients were satisfied with the adapted version. The aforementioned resource group, together with the group of user representatives, did not recommend further adjustments.

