#### Participants

In addition to the four nurses participating in the modelling phase, four new GSD-trained nurses will pilot the feasibility study (n=8). One of these four had formal postgraduate education in diabetes care, whereas the others had long experience in working with adults with T2DM. To obtain a varied picture of how the participants perceive the GSD programme, each nurse will recruit five patients with T2DM (n=40) from their general practices to participate in the web-based intervention. In addition to the inclusion criteria used in the modelling phase, participants are required to have access to the internet and Bank ID. Patients with cognitive impairment and/or severe comorbidity that would interfere with participation in the intervention will be excluded from the study.

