#### Data collection and outcomes

This phase will employ quantitative and qualitative assessments of the feasibility of the recruitment strategies, programme acceptability and satisfaction, as well as evaluation of the measures to be used in the evaluation study (table 1). The elapsed time to fill out the questionnaires, accuracy of biographic and clinical variables and handling of the format will especially be assessed. The qualitative approach includes individual interviews with patients at the end of the intervention. On the basis of findings from the questionnaires and the interviews, we will determine features of the intervention components to be valuable and those in need of further development. This information, together with recommendations from the expert group, will be used to finalise the intervention for use in the third phase of the study (see table 1).

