Diabetes-specific distress will be assessed using the 17-item version of the Diabetes Distress Scale (DDS).^53^ The DDS has four subscales: emotional burden (five items), physician-related distress (four items), regimen distress (five items) and diabetes-related interpersonal distress (three items). The responses are on a scale (1–6) from ‘not a problem’ to ‘a very serious problem’. The scale has been validated in a previous Norwegian study.^54^

In addition, clinical parameter, such as HbA1c, will be measured by a blood sample at the GP office at baseline and at the end of the intervention. Self-reported height and weight (for body mass index calculating) and medical treatment will be collected as well. The accessibility and practice of the web-based portal will be measured by asking participants to write down the number of log-ons, time spent on filling the reflection sheets, time spent on e-consultations and the number of feedbacks from the nurses.

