#### Recruitment and data collection

The study will be carried out in general practices in the western part of Norway. To accomplish the requirement of trained GSD nurses, trained nurses working in general practices will conduct the GSD intervention. Participants with T2DM to be assigned to the intervention group will therefore be recruited from the practices where the nurses are working. Participants assigned to the control group will be recruited from other general practices with employed registered nurses without the GSD training. They will continue with their regular consultations in general practice. Inclusion and exclusion criteria are the same as described for the feasibility study.

All patients considered eligible for the study will be invited by mail to participate. Those who agree to participate and return a written informed consent will be enrolled and the nurse at each selected general practice will then make an appointment with the patient to start the GSD intervention.

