#### Data analysis

The quantitative data will be analysed using SPSS V.22 (IBM Corp, Armonk, New York, USA). Descriptive statistical analyses will include frequencies, means, SDs and CIs. The effect of the intervention on outcomes will be analysed by regression analyses with the following covariates: baseline scores, age and gender.

A supplementary analysis will assess whether patient-determined goals predict change on outcomes, that is, whether patients' change goals for particular self-care activities or psychological outcomes predict greater improvements on those outcomes (eg, for analysis of frequency of blood glucose self-monitoring, we will assess the potential impact of each patient's goal, if any, for blood glucose self-monitoring). We will also explore the possibility of pooling outcome results according to whether a patient had a goal to improve that outcome, for example, estimating the pooled effect size for change in each patient's primary chosen goal.

Additional analyses will assess patient usage of and satisfaction with the intervention tools, as well as facilitators and barriers to adoption of the web-based GSD, including the quality of the communication via secure messages with the nurses. We will also examine the nurses' perceived facilitators and barriers to the adoption of the web-based GSD.

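### The Phase 3 adjustment set (baseline scores, age, gender) is thin for groups formed by practice: it leaves out diabetes duration and prior hospital education, two plausible confounders

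*Protocol article*

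**What the plan says.** **Entry.** The criterion "disease duration >3 months" is set for the modelling study (Phase 1, Adjusting the GSD programme to patients with T2DM in two steps). Phase 2, Participants, keeps it and adds to it: "In addition to the inclusion criteria used in the modelling phase, participants are required to have access to the internet and Bank ID". Phase 3, Recruitment and data collection, takes it over: "Inclusion and exclusion criteria are the same as described for the feasibility study". No upper limit on duration is given, and no criterion concerns earlier education.

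**Usual care.** The Introduction states that "most people with T2DM are offered a structured educational programme at the hospital on diagnosis to learn how to manage their disease". It does not give the waiting time, length or uptake of that programme.

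**Allocation.** Under Phase 3, Recruitment and data collection, intervention patients come from practices with GSD-trained nurses and control patients from other practices whose nurses lack that training. The limitations list and the Strengths and limitations section both acknowledge that assignment is not random.

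**Data and model.** Besides HbA1c and the questionnaires, Phase 2, Secondary outcomes, lists: "Self-reported height and weight (for body mass index calculating) and medical treatment will be collected as well". Phase 2, Data collection and outcomes, also mentions checking the "accuracy of biographic and clinical variables", without itemising them. Phase 3, Data analysis, specifies "regression analyses with the following covariates: baseline scores, age and gender".

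**The concern.** Without randomisation, the covariate set is the main statistical protection against differences that were present before the intervention. Here it consists of the baseline score, age and gender.

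Diabetes duration and prior structured education are natural candidates to add. The course described in the Introduction aims at self-management, which is also what GSD and the self-care questionnaire address and is closely tied to PAM, the primary outcome. Practices can differ in how many recently diagnosed patients they have and in how readily those patients are referred to, or take up, the course.

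The baseline score captures the level a patient has reached. It does not fully capture where the patient is in the disease course or how the score would move over the next 12–16 weeks and the six months after that. Two patients with the same baseline PAM, one recently diagnosed and one of long standing, may be on different paths. If the arms differ in that mix, part of the difference in PAM, self-care or HbA1c could be credited to GSD, or could hide a GSD effect.

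**Working it through.** **1. The plan's own figure.** Inputs from Sample size calculation: difference 6 PAM points, SD 11.1, power 90%, significance level 5%.

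n per group = 2 × (1.960 + 1.282)² × 11.1² / 6² ≈ 71.9, rounded up to 72. The stated 72 is reproduced with a two-sided test; a one-sided test would give 59. The point made here changes no sample-size input.

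**2. Standard error of the group difference.** SE = 11.1 × √(2/72) = 1.85 points. This simple form ignores any gain from baseline adjustment and any clustering by practice.

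**3. Bias from an omitted confounder.** Bias ≈ (difference between arms in the share who attended the course) × (effect of attendance on follow-up PAM). Both terms mean what is left after adjustment for baseline score, age and gender. The documents supply neither, so these values are assumptions:

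- imbalance: 0, 10 or 20 percentage points;
- effect: 3 or 6 PAM points. The upper value equals the whole target effect of GSD and is deliberately severe.

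**4. Consequences.** With b the bias:

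- two-sided error when GSD has no effect = P(|Z + b/1.85| > 1.96);
- power when the true effect is 6 and the bias works against GSD = power for a difference of 6 − b with 72 per group.

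| Imbalance | Effect | Bias b (points) | b as share of 6 | Error rate | Power |
|---|---|---|---|---|---|
| 0 | any | 0 | 0% | 5.0% | 90.0% |
| 10 points | 3 | 0.3 | 5% | 5.3% | 86.9% |
| 10 points | 6 | 0.6 | 10% | 6.2% | 83.1% |
| 20 points | 3 | 0.6 | 10% | 6.2% | 83.1% |
| 20 points | 6 | 1.2 | 20% | 9.9% | 73.7% |

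**5. What the table does not cover.** It treats prior education only. A separate contribution from duration, and the effect on HbA1c, cannot be sized from the documents.

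**The case against.** The strongest case against has five parts.

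- **The course may be over by entry.** A reader might infer that patients enter while the hospital course is still running. The documents do not support that. They say only that it is offered on diagnosis, and the three-month minimum itself excludes the period just after diagnosis. This objection stands. The point therefore rests on prior education and duration as confounders, not on a concurrent course.
- **The course is open to both arms.** Bias needs a difference between arms, and no section shows one. A reader might conclude that the GSD estimate will be distorted; the documents support only that it could be. Education completed before baseline is also partly absorbed by the baseline score. This stands and limits the size, but it does not remove the reason to adjust.
- **The data may well be collected.** A reader might infer that duration and attendance will not be recorded. That is mostly silence in a condensed article: background variables are mentioned without a list, and duration has to be ascertained to apply the entry criterion. This stands. The covariate list is different, because it is stated as a specific set and is not deferred.
- **The sizes are assumed.** A 20-point imbalance means about 0.20 × 86 ≈ 17 more attenders in one arm than in the other, and a six-point effect of the course equals everything GSD is meant to achieve. At the lower end the error rate is close to nominal. This also stands.
- **Non-random assignment is already disclosed.** It is, but a call for caution neither measures nor adjusts for a known candidate confounder.

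**Conclusion.** The point holds in a limited form. The model fixed in Phase 3, Data analysis, is too thin for a comparison of practices formed without randomisation, and diabetes duration and prior structured education are two identifiable variables that the plan's own text makes plausible confounders. No figure is wrong and no passages contradict each other.

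The size is unknown. The bias is zero if the arms are balanced, and 0.3 to 1.2 PAM points (5–20% of the six-point target) under the assumed imbalance of 10–20 points and effect of 3–6 points. The corresponding two-sided error rate is about 5.3% to 10%. These figures illustrate what could happen; they do not estimate what will. The recommendation rests on a remedy that is cheap and has to be settled before Phase 3 data collection begins.

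**What to change.** - Add diabetes duration and prior attendance at the structured hospital course (yes/no) to the covariates in Phase 3, Data analysis, for PAM and the other outcomes, including HbA1c. Record duration as a value or a date of diagnosis, not only as a check that the threshold is met. Attendance needs one baseline item.
- Show both variables by arm in the baseline table, so that readers can judge the imbalance.
- Ask about course attendance at the two follow-up visits and report it by arm, descriptively.
- Do not exclude patients who attend after baseline, and do not adjust for that attendance. GSD aims to raise activation and could itself prompt attendance, so either step would condition on a possible consequence of the intervention.

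**Cost:** one or two extra form items, with the attendance question repeated at follow-up, and two model degrees of freedom, which is small against 72 evaluable patients per group. Entry criteria and sample size are unchanged.
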